**Fig. 2 Fig2:**
[figure not shown]
Participant timeline

Sociodemographic data, characteristics of the burn (i.e., type of accident, causal agent, and percentage of body surface affected), when the burn happened, and pharmacological treatment received will be registered on an evaluation form. Participants will be instructed to maintain standard care. A trained researcher will assess and perform therapeutic procedures five times a week, once daily. Wound healing rate, pain, pruritus, skin temperature, mobility restriction, and scar quality will be analyzed.

Digital images of the burned area, skin temperature (infrared image), and pain and pruritus will be assessed daily before therapeutic procedures. Only three assessments will be analyzed: initial (before treatment), final (when re-epithelialization of the burn is complete), and one assessment between initial and final assessments (median time of treatment between initial and final assessment). After treatment and total wound closure, mobility and scar quality will be assessed using the adheremeter and Vancouver Scale, respectively.

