#### Sample size {14}

Randomized controlled trials conducted with participants with burn wounds are scarce, hindering the calculation of the effect size. Thus, a conservative effect size (0.5), 80% power, and 95% probability (*α* = 0.05) were used for the primary outcome (re-epithelialization rate), generating a sample size of 30 participants (three groups of ten participants). The sample size for repeated measures ANOVA was calculated using the G* Power 3.1.0 software (Christian-Albrechts-Universitat, Kiel, Germany). Considering a possible sample loss of 30%, we intend to recruit 39 participants.

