### Assignment of interventions: allocation

#### Sequence generation {16a}

The online software randomization.com will be used to allocate participants by blocks into three parallel groups (1:1:1) of 13 subjects: RLG, which will receive photobiomodulation using red LED; ILG, which will receive photobiomodulation using infrared LED; and SG, which will undergo a simulated application of LED therapy.

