## Statistical methods

### Statistical methods for primary and secondary outcomes {20a}

Outcome variables will be re-epithelialization rate, presence and intensity of pain and pruritus, local skin temperature, and scar mobility and quality. Groups will be considered independent variables. Statistical analysis will be performed according to intention-to-treat principles. Descriptive analyses and histogram inspections will determine data normality. Between-group differences and 95% confidence intervals (95% CI) will be calculated using linear mixed models and group, time, and group-versus-time interaction terms. A first-order autoregressive covariance matrix will be considered. Group and time will be considered fixed factors, and participants the random factors. A Q-Q plot will be performed for all variables to consistently and similarly confirm the normality of residues between groups. The SPSS software version 20.0 (IBM SPSS Corp., Armonk, NY) will be used for data analysis.

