### Methods for additional analyses (e.g., subgroup analyses) {20b}

Not applicable. We do not plan to conduct subgroup or adjusted analyses.

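### The model for pain, pruritus and skin temperature uses the pre-treatment value as an outcome, not as a baseline adjustment, so precision is lost and chance imbalance stays in the contrasts

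*Protocol article*

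**What the plan says.** The section on statistical methods for primary and secondary outcomes {20a} sets the model: "Between-group differences and 95% confidence intervals (95% CI) will be calculated using linear mixed models and group, time, and group-versus-time interaction terms". It adds "Group and time will be considered fixed factors, and participants the random factors" and "A first-order autoregressive covariance matrix will be considered".

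The participant timeline {13}, in the text below Fig. 2, fixes which times enter: "Only three assessments will be analyzed: initial (before treatment), final (when re-epithelialization of the burn is complete), and one assessment between initial and final assessments". The same text shows that the symptom and temperature outcomes have a genuine pre-treatment value: "Digital images of the burned area, skin temperature (infrared image), and pain and pruritus will be assessed daily before therapeutic procedures".

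The section on additional analyses {20b} says "We do not plan to conduct subgroup or adjusted analyses". Sequence generation {16a} gives the arm size: "allocate participants by blocks into three parallel groups (1:1:1) of 13 subjects". No section names the initial value as a covariate or requires the arms to share a mean at the initial assessment. Section {20a} also does not say whether the reported between-group difference is the difference at a visit or the group-by-time (change) contrast.

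**The concern.** With group, time and their interaction as categorical fixed effects, and the initial assessment as one of the times, the model estimates a separate mean for each arm before anyone has been treated. Randomization makes the true means equal at that time. The model does not use this fact, so the most informative covariate in the data set does no adjusting.

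Two contrasts could be reported. The difference at a visit carries part of any chance baseline gap forward. The difference in change subtracts the whole gap, which over-corrects unless the correlation between initial and later values is 1. At 13 per arm such gaps are ordinary. At stake are the width of the intervals for pain, pruritus and temperature, and how an observed LED-sham difference should be read when the arms happened to start apart.

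**Working it through.** **Scope.** The points below concern pain, pruritus and skin temperature. The percentage re-epithelialized is zero at the start by construction, and scar mobility and scar quality are measured only after healing.

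**The plan's own figure.** The only stated calculation is the sample size, from "a conservative effect size (0.5), 80% power, and 95% probability". Reading 0.5 as Cohen's f in a between-factor repeated-measures ANOVA with 3 groups and 3 times, and assuming a correlation of 0.5, λ = 0.25 × 30 × 3 / (1 + 2 × 0.5) = 11.25. Power is then 0.817 at N = 30, which matches the stated 30. That calculation is for the primary outcome and is not affected here. The protocol states no precision for the symptom and temperature outcomes.

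**Inputs.** Arm size n = 13 (sequence generation), or 10 after the losses allowed for (sample size section). The baseline-to-follow-up correlation ρ is not given, so 0.3, 0.5 and 0.7 are assumed. Equal variances over time are assumed unless stated otherwise.

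**Step 1: size of chance baseline gaps, in SD units.**
- SE = √(2/n) = √(2/13) = 0.39, so the 95% range is ±0.77.
- P(gap above 0.5 SD for one LED-sham pair) = 2 × (1 − Φ(0.5/0.392)) = 0.20.
- P(at least one of the two LED arms differs from sham by that much) is about 0.34, by simulation.
- With 10 per arm, SE = 0.45 and the single-pair probability is 0.26.

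**Step 2: effect of a 0.5 SD gap on each contrast.** The visit difference shifts by 0.5ρ. The change contrast shifts by 0.5(1 − ρ) in the opposite direction. The adjusted contrast does not shift.

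**Step 3: relative variance of the contrasts** (visit difference = 1; change = 2(1 − ρ); adjusted = 1 − ρ²).

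| ρ | Change variance | Adjusted variance | SE reduction vs visit difference | SE reduction vs change | Shift, visit | Shift, change |
|---|---|---|---|---|---|---|
| 0.3 | 1.4 | 0.91 | 1 − √0.91 = 5% | 1 − √(0.91/1.4) = 19% | +0.15 | −0.35 |
| 0.5 | 1.0 | 0.75 | 13% | 13% | +0.25 | −0.25 |
| 0.7 | 0.6 | 0.51 | 29% | 8% | +0.35 | −0.15 |

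**Step 4: the protocol's covariance.** Under first-order autoregression alone, the initial-to-final correlation is the square of the adjacent one. Adjacent values of 0.3, 0.5 and 0.7 become 0.09, 0.25 and 0.49, and the large-sample SE reduction against the final-visit difference falls to about 0.4, 3 and 13%. A participant random effect would slow that decay.

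**Step 5: simulation, 13 per arm, adjacent correlation 0.7** (SE in SD units).

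| Visit | Visit difference | Change | Adjusted |
|---|---|---|---|
| Middle (ρ = 0.7) | 0.391 | 0.304 | 0.284 |
| Final (ρ = 0.49) | 0.391 | 0.395 | 0.346 |

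At the final visit, the correlation of the estimate with the baseline gap was +0.49 (visit difference), −0.51 (change) and 0.00 (adjusted). With adjacent correlation 0.3 (ρ = 0.09 at the final visit), the SEs were 0.393 for the visit difference, 0.526 for change and 0.397 for the adjusted contrast. Adjustment then costs about 1% against the visit difference.

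**Step 6: does the form of adjustment matter?** Suppose spread shrinks as wounds close, with assumed SDs of 1, 0.7 and 0.4 at the three times. A common-baseline-mean model that keeps a homogeneous autoregressive covariance then has a final-visit SE of 1.00, 1.01 and 1.05 times that of the visit difference, for adjacent correlations of 0.3, 0.5 and 0.7. With SDs of 1, 0.6 and 0.25 the ratios are 1.02, 1.11 and 1.35. A freely estimated baseline slope for that visit shows no such loss: its large-sample ratios are 1.00, 0.97 and 0.87 in both cases (√(1 − ρ²) with ρ = 0.09, 0.25 and 0.49).

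**The case against.** The strongest reply is that nothing here is invalid. A group-by-time mixed model is conventional, its contrasts are unbiased under randomization, and its intervals already allow for chance baseline imbalance. That stands. A reader might infer from the 20% and 34% figures that the plan yields biased results or a raised error rate. It does not: those figures describe ordinary sampling variation at 13 per arm. What is lost is precision, together with freedom from bias conditional on the imbalance actually observed.

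A second reply is that the protocol does not name the reported contrast, so it cannot be said that the baseline gap is simply carried into the result. This also stands, since the change contrast subtracts the gap. It does not remove the point, because both contrasts remain correlated with the gap, in opposite directions.

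Third, a reader might take the sentence in {20b} as a ban on baseline adjustment. It stands under additional analyses and need not govern the main model in {20a}. The wording is ambiguous, and that is all that can be said.

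Fourth, the gain may be small where it matters most. The final assessment is at complete healing, and a weak link to the initial value is plausible there. This stands as a limit on size against the visit difference. Against the change contrast, a weak correlation makes the gain larger.

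Finally, the choice of parameterization might be thought a matter for an analysis plan that is not shown. But the article itself fixes the analyzed times, fixed effects, random factor and covariance, and a better use of data already collected is available.

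**Conclusion.** The point holds as one of efficiency and of conditional bias, for pain, pruritus and skin temperature only. The planned model makes no use of the initial value as an adjustment. Whichever contrast is reported is generally less precise than a baseline-adjusted one. The exceptions are a correlation near zero, where the visit difference is as good, and one near 1, where the change contrast is as good.

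The expected reduction in standard error is about 5 to 29% against the visit difference and 19 to 8% against the change contrast, for ρ from 0.3 to 0.7. These figures rest on assumed correlations, equal variances and large-sample formulas. At the final visit the gain over the visit difference could be close to nil. The documents support neither a claim of systematic bias nor any effect on the primary outcome or the sample size. The change is worth making, but the trial's validity does not depend on it.

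**What to change.** For pain, pruritus and skin temperature, model only the middle and final assessments as outcomes. Use group, time and group-by-time as fixed effects, and add the outcome's own initial value and its interaction with time, so that the baseline slope may differ by visit. Report the LED-sham difference with its 95% interval at each of the two post-baseline assessments.

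If a model with one common baseline mean is preferred, two conditions apply. The constraint needs constructed post-baseline group indicators, because dropping the group term while keeping group-by-time re-expresses the same cell means. The homogeneous autoregressive covariance should also be replaced by an unstructured or heterogeneous-variance one, for the reason in step 6. The two forms should not be treated as interchangeable.

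In {20b}, state that the exclusion of adjusted analyses does not cover adjustment for an outcome's own initial value. Record the change before unblinding.

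Cost: no new data, a few degrees of freedom, and a negligible loss of precision if the correlation is near zero. A participant with only an initial value adds nothing to the covariate form, so the number of such participants should be reported by arm.

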#### Primary outcome measures

##### Re-epithelialization rate

The percentage of healed skin tissue (re-epithelialization rate) and the number of days between the start of treatment and total healing process will be assessed using digital images of the burned region. These images will be captured daily from before treatment to follow-up of the re-epithelialization process. A digital camera (Sony Cyber-Shot Dsc-W800, 20.1 megapixels, Brazil) will be positioned on a tripod, parallel to the ground and perpendicularly fixed at a distance of 30 cm from the area to be treated. If the participant cannot stand, images will be captured on a stretcher assuring the same distance and a 90° angle between the area and the camera. The photograph will be captured on a white background with indirect artificial lighting.

Re-epithelialization rate will be assessed by counting the days until complete healing and monitoring the wound area during protocols (ImageJ® software, version 1.36 b). The crust area on the wound edge will be measured using digital image analysis, according to Gabison et al. [19]. The software converts the selected area to cm^2^ by associating the known dimension of the photographed object, area of interest, and the respective number of pixels. Healing will be assessed using a glossary of healing evolution based on the pressure ulcer assessment scale proposed by Bates-Jensen, Vredevoe, and Brecht [20].

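### The planned AR(1) model forces equal variance on three assessments where percent healed can vary only at the middle one, so its midpoint intervals are too narrow; for pain and itch the effect is possible but not forced

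*Protocol article*

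**What the plan says.** The protocol article's section on statistical methods for primary and secondary outcomes {20a} says that between-group differences and their 95% confidence intervals will be "calculated using linear mixed models and group, time, and group-versus-time interaction terms". It adds "A first-order autoregressive covariance matrix will be considered" and "Group and time will be considered fixed factors, and participants the random factors". It names no heterogeneous version of the structure and no alternative to it.

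The text under Fig. 2 (participant timeline) fixes the time points: "Only three assessments will be analyzed: initial (before treatment), final (when re-epithelialization of the burn is complete"), plus one between them, placed at the "median time of treatment between initial and final assessment".

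The primary outcome section defines what is measured: "The percentage of healed skin tissue (re-epithelialization rate) and the number of days between the start of treatment and total healing process". It also mentions "monitoring the wound area during protocols". The scar outcomes are taken once: "After treatment and total wound closure, mobility and scar quality will be assessed using the adheremeter and Vancouver Scale".

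**The concern.** A first-order autoregressive matrix has a single variance parameter. A participant random intercept adds the same constant at every assessment, so the marginal variance stays equal over time. Yet two of the three assessments are defined by the state of the wound: untreated at the start, closed at the end. For percent healed, neither can show any spread between participants.

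The fitted variance is then an average of one real variance and two zeros. The midpoint is the only assessment at which the arms can differ on percent healed, and that is where the interval comes out too short. The trial could report a benefit of LED on a primary outcome measure from a comparison whose false-positive rate is several times the nominal 5%.

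**Working it through.** **Inputs from the protocol.** Three groups of 13 (10 per group before the allowance for loss); three analysed assessments; homogeneous AR(1) with a participant random factor. The protocol gives no standard deviations (SDs), so those below are assumptions, except that percent healed has zero SD at the start and at closure by definition. The protocol states no figure on this point to reproduce.

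**Formulas.** With little correlation between assessments, the common SD that AR(1) estimates is close to the root mean square of the three true SDs:

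- pooled SD = sqrt[(s1² + s2² + s3²)/3]
- standard error (SE) ratio at assessment j = pooled SD / sj, because the true SE of a group difference is sj × sqrt(2/n)
- actual error of a nominal 5% test ≈ 2 × P(Z > 1.96 × ratio)

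**Percent healed, SDs 0 / s / 0.**

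- AR(1) alone: pooled SD = s × sqrt(1/3) = 0.577s. Error = 2 × P(Z > 1.96 × 0.577) = 2 × P(Z > 1.13) = 0.258. The ratio does not depend on s.
- AR(1) plus random intercept, negative autocorrelation allowed: the first and last values have no spread, so the fit runs towards a singular solution that treats them as one quantity. The average is then over two variances, (0 + s²)/2, giving a ratio of sqrt(1/2) = 0.707. Error = 2 × P(Z > 1.39) = 0.166.
- Simulation with no group effect, 10 or 13 per group: AR(1) alone gave ratios of 0.56 to 0.57 and rejection of 23% to 25%, and about 28% in a separate run (a run of only 120 replicates gave 18%). With the random intercept, most runs gave a ratio of about 0.70, with rejection of 14% to 19% across runs. Using each assessment's own variance gave about 5%.

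**Wound area, assumed SDs 20 / 12 / 0 (closure is zero by definition).** Pooled SD = sqrt[(400 + 144 + 0)/3] = 13.5. Ratios: baseline 13.5/20 = 0.67, midpoint 13.5/12 = 1.12. Simulated rejection at baseline was 14% to 21%.

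**Pain or itch, assumed SDs.**

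| SDs (start / middle / closure) | Pooled SD | Ratios by formula | Simulated ratios | Simulated rejection |
|---|---|---|---|---|
| 2.5 / 2 / 0.7 | sqrt(10.74/3) = 1.89 | 0.76 / 0.95 / 2.70 | 0.75 / 0.94 / 2.7 | about 14% / 6–9% / 0% |
| 2 / 2 / 0.7 | sqrt(8.49/3) = 1.68 | 0.84 / 0.84 / 2.40 | 0.82–0.83 / 0.82–0.83 / about 2.36 | 8–12% / 10–11% / 0% |
| 2 / 2 / 1.5 | sqrt(10.25/3) = 1.85 | 0.92 / 0.92 / 1.23 | 0.92 / 0.92 / 1.22 | about 7% / 6% / 3% |

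**Temperature, assumed equal SDs 1 / 1 / 1.** Ratios 0.99 to 1.00 and rejection of about 3% to 6%, so there is no distortion.

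**Single-measurement outcomes.** Scar mobility, the Vancouver score and days to healing have one value per participant, so no covariance over time applies.

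**The case against.** **The wording is soft, and covariance choice often belongs in the analysis plan.** The text says the structure will be considered, and residual plots are planned. But the protocol does name a structure, offers no other, and fixes the three assessments. For percent healed the clash follows from those statements alone. It is not a complaint about missing detail.

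**The root cause is the choice of assessments.** This stands. An unstructured matrix cannot be fitted to percent healed when two of its three variances are zero. Changing the covariance alone would not rescue the primary outcome; the timeline text must change too.

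**The size is unstable.** This also stands in part. The error depends on whether negative autocorrelation is allowed and on how the near-singular fit is handled, so a range is the honest statement. Every calculation puts it well above 5%.

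**Tempting stronger readings that the document does not support.**

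- A reader might infer that none of the outcomes can have equal variance. That is forced only for percent healed and wound area. Pain and itch probably bunch near zero at closure, but nothing in the protocol requires it, and the mild scenario above does little harm.
- A reader might extend the error to temperature. Nothing in the protocol rules out equal variance there.
- A reader might argue that participants' differing healing times leave no common lag correlation. Healing time spans both gaps, not one. The 7 to 21 days in the background section describe burns in general, not time from the start of treatment. An unstructured matrix also imposes one covariance on everyone, so it would not answer that complaint.

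**Conclusion.** The point holds for the primary outcome on the protocol's own definitions. For percent healed, the planned model gives a midpoint standard error of about 0.57 to 0.70 of the truth and an error of roughly 15% to 28% in place of 5%. The ratio does not depend on the midpoint SD. It does assume that the final value is taken at complete closure, as the timeline states. The intervals that are far too wide at the start and at closure matter little for this outcome, because no group difference can exist there.

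If wound area is the modelled response, the baseline interval is too narrow (ratio about 0.67), on assumed SDs. For pain and itch the effect is conditional: ratios run from 0.92 / 0.92 / 1.22 to 0.75 / 0.94 / 2.7 over the SDs tried. In the worse case the comparison at closure loses almost all power. Temperature is not shown to be affected, and the scar outcomes and days to healing are outside the issue. The plan should be changed before analysis.

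**What to change.** - **Percent healed.** Leave the start and closure assessments out of the model. Compare arms at one pre-specified day, counted from the start of treatment and the same for all participants, using the photographs already taken daily and that day's own variance. Participants closed by then count as 100%. Choose a day on which a session is held and before most wounds have closed, so that the outcome still varies. Compare days to healing alongside it, as a single value per participant. If wound area is the response, compare it at the same day in the same way.
- **Pain and itch.** Replace AR(1) plus random intercept by an unstructured 3 × 3 residual covariance with Satterthwaite degrees of freedom and no separate random intercept. The same can be used for temperature; it does no harm if the variances are equal.

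**Cost.** Edits to the timeline text under Fig. 2 and to section {20a}, and six covariance parameters in place of three. No new data are needed.

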### Interim analyses {21b}

An interim analysis will be performed on the primary endpoint after randomization and complete re-epithelization of 50% of participants. An independent and blinded statistician will perform the analysis and report to the independent data and safety monitoring committee (DSMC). The DSMC will have unblinded access to data and discuss the results with the steering committee. Then, the steering committee will decide on the trial continuation and report to the central ethics committee. The trial will end if any severe damage is identified in the experimental groups. The trial will not stop due to futility unless the DSMC advises otherwise during the course of safety monitoring. In this case, the DSMC will discuss the possible stop of the trial with the steering committee.

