### Oversight and monitoring

#### Composition of the coordinating center and trial steering committee {5d}

This single-centered trial will be supervised by the clinical research center and ethics committee of the Federal University of Paraíba. The principal investigator will coordinate the trial, and two researchers (one coordinator and one associate researcher) will ensure quality control according to the principle of good clinical practice. These two researchers will monitor the study progress, verify if the protocol is being followed, and submit the study status and review suggestions to the principal investigator, who will report to the ethics committee and organize discussions about the study protocol and data management. The principal investigator, the assessor, and the quality control coordinator will form the data management team, responsible for maintaining the database and confirming data accuracy, completeness, entry, and analysis.

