#### Composition of the data monitoring committee, its role, and reporting structure {21a}

No data monitoring committee was appointed due to the low burden and minimal risks; therefore, researchers will be responsible for data monitoring. Periodically, the quality control team will randomly monitor the assessment and application of the intervention in all groups without prior notice.

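### The interim analysis depends on a monitoring committee that another section says was never appointed, and on either reading comparative efficacy results reach the people running the trial

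*Protocol article*

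**What the plan says.** All references are to the protocol article.

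- **What is looked at and when** (Interim analyses {21b}): "An interim analysis will be performed on the primary endpoint after randomization and complete re-epithelization of 50% of participants".
- **Who receives it** (same section): "An independent and blinded statistician will perform the analysis and report to the independent data and safety monitoring committee (DSMC".
- **Where the results go next** (same section): "The DSMC will have unblinded access to data and discuss the results with the steering committee".
- **Who decides** (same section): "Then, the steering committee will decide on the trial continuation and report to the central ethics committee".
- **Grounds for stopping** (same section): for harm, "The trial will end if any severe damage is identified in the experimental groups"; for futility, "The trial will not stop due to futility unless the DSMC advises otherwise during the course of safety monitoring". Efficacy is not mentioned as a ground, either way.
- **Whether the committee exists** (item {21a}, the section on the monitoring committee): "No data monitoring committee was appointed due to the low burden and minimal risks; therefore, researchers will be responsible for data monitoring".
- **Who handles the data** (Composition of the coordinating center and trial steering committee {5d}): "The principal investigator, the assessor, and the quality control coordinator will form the data management team".
- **Error rate** (Sample size {14}): α = 0.05, with no share set aside for an interim look.

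**The concern.** Whether an independent committee exists is a basic fact of the protocol, and two current sections give opposite answers. Everything in the interim section hangs on that committee: it holds the unblinded access, it receives the report, and futility stopping requires its advice. Without it, the text names no one but the trial's own researchers to take its place.

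Two things are at stake. The first is knowledge of the comparative result. A team that knows halfway through which arm is ahead can, without intending to, change how it recruits, how it encourages attendance, how it handles withdrawals, and whether it continues. The trial relies on traced photographs for its primary outcome and on participant-reported pain and itch, so it has good reason to keep that knowledge away from those running it. The second is the error rate. The look is at the efficacy endpoint and feeds a continuation decision, but the text does not say whether a favourable result may be acted on.

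**Working it through.** **1. The two sections side by side.**

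| Question | Interim analyses {21b} | Data monitoring committee {21a} |
|---|---|---|
| Is there a monitoring committee? | Yes, independent | None appointed |
| Who monitors the data? | The committee, with unblinded access | The researchers |
| Who advises on futility? | The committee | Nobody named |

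*If {21b} is right*, the committee discusses the results with the steering committee, and no limit on what is shared is described. *If {21a} is right*, the report has no independent recipient, monitoring falls to the researchers, and the steering committee still decides on the result. In both cases the comparative result reaches trial leadership.

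**2. The plan's own sample size.** Inputs from Sample size {14}: effect size f = 0.5, α = 0.05, power 80%, three groups, repeated-measures ANOVA. Three analysed assessments (m = 3) come from Participant timeline {13}. The correlation between measurements is not stated; ρ = 0.5 is assumed. With the between-groups option:

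λ = f²·N·m / (1 + (m − 1)ρ) = 0.25 × 30 × 3 / (1 + 2 × 0.5) = 22.5 / 2 = 11.25, on (2, 27) degrees of freedom.

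Power is 0.817, and N = 30 is the smallest total in equal groups that reaches 80%. The stated figure reproduces, with the whole 0.05 given to one final test. Recruitment is 30 × 1.3 = 39.

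**3. Size of the interim.** 0.5 × 39 = 19.5, so about 20 participants, or 20/3 ≈ 6 to 7 per arm.

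**4. Error rate if efficacy could be claimed at both looks.** Assume a two-sided 5% test (|Z| > 1.96) at information fraction t and again at the end. The two statistics are bivariate normal with correlation √t:

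overall error = 1 − P(|Z₁| < 1.96, |Z₂| < 1.96).

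| Information fraction t | √t | Overall type I error |
|---|---|---|
| 0.5 | 0.707 | 0.0831 |
| 20/39 = 0.513 | 0.716 | 0.0827 |
| 20/30 = 0.667 | 0.816 | 0.0770 |
| 20/27 = 0.741 | 0.861 | 0.0738 |

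The last two rows cover the case in which about 20 healed participants are set against a final data set reduced by the planned 30% loss (30 evaluable, or 39 × 0.7 ≈ 27). Simulating a three-group F test (200,000 runs) gave 0.086 with 5 then 10 per arm and 0.083 with 7 then 13 per arm.

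**5. Error rate if efficacy cannot be claimed at the interim.** Stopping only for harm or futility gives no extra chance to declare benefit, so the final test at 0.05 keeps the error rate at no more than 0.05.

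**6. Thresholds that would hold 5% with one look at t = 0.5.**

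| Rule | Interim p | Final p |
|---|---|---|
| Haybittle-Peto | < 0.001 | about 0.0498 (overall 0.0502 if the final is left at 0.05) |
| O'Brien-Fleming | < 0.0052 | 0.0480 |
| Pocock | < 0.0294 | 0.0294 |

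**The case against.** The strongest reply is that little follows beyond an editing slip. Four parts of it deserve an answer.

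*The error-rate argument is hypothetical.* This stands. The interim section names harm and futility, not efficacy, and stopping on those grounds does not inflate type I error. A reader might infer that the trial as planned runs at 8.3%. The document does not support that: the figure holds only if a favourable interim result can be claimed, which the text neither allows nor rules out.

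*Numerical boundaries belong in the analysis plan.* This also stands, and the absence of a number is not the point. Whether a committee exists, and who sees unblinded results, cannot be left to a document that would itself have to choose between the two sections.

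*The look has a purpose and rules.* True. A reader might infer that harm is the only stopping ground, or that the look serves no decision. In fact there is a discretionary futility clause and a stated continuation decision. What is lacking is any statement on efficacy.

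*Blinding is not shown to be broken.* Partly true. Group-level results do not reveal an individual's allocation, and participants, assessors and analysts are to be blinded. It is tempting to read the data management team in {5d} as putting unblinded results in the assessor's hands. That section does not say the team receives interim results, nor that the assessor sits on the steering committee. Likewise, a blinded statistician serving an unblinded committee is unexplained but not impossible, for example with coded arms. The exposure that the text does create is that of trial leadership to the comparative result.

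**Conclusion.** The point holds. The two sections contradict each other in current text, the interim procedure cannot be carried out as written, and under either reading comparative efficacy results at about 20 of 39 participants (6 to 7 per arm) reach those who run the trial and decide on its continuation. This conclusion needs no assumption and no unseen document.

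The effect on error is conditional. It is 5% if efficacy stopping is excluded. If a 5% test could be acted on at both looks, it is about 8.3% at half information, or 7.4% to 7.7% if the planned loss makes the interim a larger share of the final data. The protocol should say which case applies. Recruitment is reported as under way (Trial status), so this needs settling before the halfway look: knowledge of a comparative result cannot be withdrawn.

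**What to change.** 1. Make Interim analyses {21b} and Composition of the data monitoring committee {21a} agree on whether a committee exists and who sees unblinded data.
2. Then choose one of two courses:
   - *Drop the comparative look at the primary endpoint.* The cost is the futility route that it now offers.
   - *Keep it*, with comparative results withheld from the steering committee and the researchers, who receive only a recommendation. The cost is that an independent recipient must actually be appointed.
3. If the look is kept, state that it cannot lead to an efficacy claim, with the final test at 0.05. If it can, require p < 0.001 at the interim and test at about 0.05 at the end (overall error 0.0502). The cost in power is negligible, though so strict a threshold will seldom be met with about 20 participants.
4. The statements bearing on stopping for harm in {21b}, {21a} and Adverse event reporting and harms {22} should be reconciled by the sponsor. No particular harm rule is proposed here.

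Apart from appointing a recipient, if the look is kept, this is a change of protocol wording, notified through the amendment route that the protocol already describes. It needs no additional participants.
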